### Trial interventions

This trial included an experimental educational intervention ISS [18,21], which means training in the actual patient care unit (in other words, the labor room and operating theatre). The experimental intervention in the present trial was pre-announced ISS. We planned to conduct announced ISS training, as the complexity of conducting unannounced ISS sessions with the involvement of health-care professionals on a larger scale is unrealistic taking into consideration work schedules and the daily clinical work activities. Training of the control group (OSS) took place in training rooms that were set up for the occasion in the hospital, but away from the actual patient care unit.

The simulated scenarios applied in the trial were contained in a full training day. The development of the curriculum for the training day was based on an instructional design approach [38,39] and was developed and pilot tested by a local multi-professional working committee. In January 2012 this working committee was appointed by the managerial groups of the departments of anesthesia and obstetrics and consisted of representatives from all the health-care professionals who will participate in the trial. This working committee developed aims and objectives based on the principles of Blooms taxonomy [40], and the aims and objectives were approved by the management groups. The simulated scenarios in ISS and OSS were designed in a way that involved both the labor room setting and the operating theatre, to specifically focus on the patient journey and the communication amongst health-care professionals during patient transfers, where many different health-care professionals and different medical disciplines are involved. This approach to training was chosen based upon previous experience with obstetric simulation-based training conducted in the obstetric department [32,41] and was designed in accordance with the overall plan of strategy of the obstetric department and the anesthesia department, Juliane Marie Centre for Children, Women and Reproduction, Rigshospitalet [42].

In the labor room, a simulated patient acted as the patient. In the operating room, a full body interactive birthing simulator, a SimMom, was the patient [43]. The SimMom simulator offers the functionality required for training in a wide range of midwifery, obstetric and anesthesia skills, and the anatomy and functionality of the SimMom allows for multi-professional training of labor and delivery management. Standardized clinical simulated scenarios were designed and, combined with pre-programmed scenarios on the SimMom, this allowed for standardized training. The educators were recruited from the local working committee, and all educators were trained to run the scenarios in a standardized way and in facilitating the simulation scenarios and debriefing the participants.

In addition, the training day also included some video-based, case-based and lecture-based teaching sessions. Also, on the simulation days, data related to the trial were collected in the form of written multiple choice questions (MCQ), questionnaires on subjective stress and salivary cortisol samples (Table 1). Training days were scheduled into the individual employee’s working plan. Figure 1 gives an overview of the randomization and intervention procedure as well as outcomes.

**Table 1 T1:** Time schedule of measurements

**Individual measurements**							**Team measurements**	
**Multiple choice questionnaire**	**Safety attitudes questionnaire**	**Stress**-**trait anxiety inventory**	**Cognitive appraisal**	**Test for salivary cortisol**	**Intrinsic motivation inventory**	**Evaluation questionnaire**	**Team emergency assessment measure**	**Selected clinical measures**
Training day start of day	4 weeks before training day	Training day before 1. simulation and twice after	Training day before 1. simulation and twice after	Training day before 1. simulation and three times after	1 week after training day	1 week after training day	Training day	Training day
							1. simulation: video recordings. Video assessment by independent assessors.	1. simulation: video recordings. Video assessment by independent assessors.
Training day end of the day	4 weeks after training day	Training day before 2. simulation and twice after	Training day before 2. simulation and twice after	Training day before 2. simulation and three times after			Training day	Training day
							2. simulation: video recordings. Video assessment by independent assessors	2. simulation: video recordings. Video assessment by independent assessors

**Figure 1 F1:**
[figure not shown]
**Randomized trial of ‘*****in situ *****simulation’ (ISS) versus ‘off site simulation’ (OSS): randomization, intervention and outcome measurements.**

### Blinding

The participants and the educators providing the educational intervention, and the assessors observing and assessing videos, were not blinded to the intervention. The data managers, statisticians and investigators drawing conclusions will be blinded to the allocated intervention groups.

### Measurements and assessment of outcomes

Table 2 provides an overview of the variables, outcomes and accompanying statistical analyses. Table 2 is inspired by the SPIRIT 2013: Explanation and elaboration: guidance for protocols of clinical trials [44]. See Table 1 for the time schedule for obtaining measurements.

**Table 2 T2:** **Variables**, **research hypothesis**, **outcome measures and methods of statistical analysis**

**Variable/****outcome on individual level ****(N ****= ****100)**	**Research hypothesis**: **experimental group versus control group**	**Outcome measure**	**Type of variable**	**Methods of statistical analysis**
**Primary outcome**				
Multiple choice questions	Improvement occurs in the experimental group	Percentage correct in 40 multiple choice questions	Will be analyzed as interval data, a Gaussian distribution is expected	Parametric techniques
				ANOVA
**Exploratory outcome**				
Safety Attitudes Questionnaire	Increased score in the experimental group	33 items on a 5-point scale. Divided into 6 dimensions	Will be analyzed as interval data, a Gaussian distribution is expected	Parametric techniques
				ANOVA
		Data are converted to the 100-point scale		Chi-square tests
Stress-Trait Anxiety Inventory Baseline	Increased peak score in the experimental group	Inventory 20 item (interval 20 to 80).	Will be analyzed as interval data, a Gaussian distribution is expected	Parametric techniques
				ANOVA
Stress-Trait Anxiety Inventory 1				
Stress-Trait Anxiety Inventory 2				
Cognitive appraisal A Baseline	Increased peak score in the experimental group	Likert scale 1 (10 point)/Likert scale 2 (10 point) (interval 1/10 to 10)	Ordinal data	Non-parametric techniques
Cognitive appraisal 1				Mann Whitney U test
Cognitive appraisal 2				
Test for salivary cortisol Baseline	Increased salivary cortisol level from baseline to peak in the experimental group	Cortisol level in nmol/l	Interval data	Parametric techniques
Test for salivary cortisol 1				ANOVA
Test for salivary cortisol 2				
Test for salivary cortisol 3				
Evaluation questionnaire	Increased positive evaluation in the experimental group	20 questions on a 5-point Likert scale	Ordinal data	Non-parametric techniques
				Treated as ordinal data at the item level
Intrinsic Motivation Inventory	Increased score in the experimental group	Task evaluation inventory 22 items on a 7-point scale. Divided into 4 dimensions	Ordinal data	Non-parametric techniques
				Mann Whitney U test
**Variables on team**-**level**				
**(N ****= ****10 teams)**				
Team Emergency Assessment Measure	Improved outcome in the experimental group	Video assessment on a 5-point scale (0 to 5) of 11 questions (0 to 44) 10 points scale for global rating of the team	Ordinal data	Non-parametric techniques
				Mann Whitney U test
Selected clinical measures	Improved outcome in the experimental group	Minutes before decision making about operation, minutes before operation initiated. Medication given yes/no	Interval data	Parametric techniques

The table is inspired by SPIRIT 2013: Explanation and elaboration: guidance for protocols of clinical trials [44]. ANOVA, analysis of variance.

### Primary outcome

The primary outcome is knowledge test results from MCQs. The mean values of results of the MCQs of the experimental and control group were tested at the end of the training day and will be compared.

Previous research on knowledge testing has found that written tests are able to predict results in performance-based testing [45,46]. The argument for applying the MCQ is that it is feasible to test many participants in a relatively short time and at low costs [45]. Previously used MCQ tests and 'knowledge of skills test' [13,32] were used for inspiration, when constructing this new MCQ.

The MCQs were created as a 'one-best-answer' item format with three to five options, which requires the participants to select the single best response [47,48]. The content of the MCQs were based on aims and objectives developed by the multi-professional working group appointed by the management and has been tested amongst all health-care professional in this local working group. The content validity was further tested among specialized obstetricians and specialized obstetric anesthesiologists. Subsequently, the MCQs were tested among midwifery students, medical students, trainee doctors and specialized obstetricians and specialized obstetric anesthesiologists from other hospitals and were found to be construct valid. During the statistical analysis, some items in the MCQ needed to be deleted. The description of development and results of the MCQs used in this trial will be reported in another publication.

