### Randomization

Randomization was done by the Copenhagen Trial Unit, using a computer-generated allocation sequence concealed to the investigators. The randomization was conducted in two steps. The participants were individually randomized into the experimental group (ISS) or the control group (OSS). The allocation sequence was stratified according to health-care professional groups in order to resemble authentic teams and according to the days they were available for training. After individual randomization, the participants in either group (ISS and OSS) were randomized into five teams each.

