### Exploratory outcomes

The “Safety Attitudes Questionnaire” (SAQ) consists of 33 items on a five-point scale that is divided into six dimensions. SAQ was applied approximately 1 month prior to and approximately 1 month after the training day. The mean values on six different dimensions of the SAQ results from the experimental and control group will be compared 1 month after the training day. SAQ is an inventory used in several countries and also applied and validated in a Scandinavian context, and previously tested in Denmark [49-51].

Salivary cortisol (reflecting the hypothalamic-pituitary-adrenal axis activity) was used as a biological marker of stress levels. The Sarstedt Cortisol Salivette Device, provided by Neogen corporation [name] Product no. 402710, was used The analysis will be a duplicate analysis based on the Elisa Technique 405 nm, where 100 ul sample will be extracted and 50 ul in duplication will be used in the ELISA kit. Eight standards in ranges from 0.04 ng/ml up to 10ng/ml will be used in the assay together with a blanc control. The microtitterplate will be read in a dual wavelength set at 450 nm and 650 nm. In calculation of the data, the blanc background will be subtracted from all absorbance values before a non linear fit to the standard curve will be calculated.

The salivary cortisol sample was obtained before the simulation (baseline) and three times in relation to the simulations. The cortisol response will be measured as increased salivary cortisol from individual baseline to peak, and mean response values in the experimental and control group will be compared.

State-Trait Anxiety Inventory (STAI-1) was administered before the simulations started (baseline) and twice following the simulations [52,53]. It will reflect the subjective stress response. The peak level of subjective stress response will be used and mean values in the experimental and control group will be compared.

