### Sample size estimation adjusted for clustering

As the intervention was delivered in teams (clusters), observations on participants in the same team were likely to be correlated. Hence the effective sample size was less than that suggested by the actual number of individual participants. The reduction in effective sample size depends on the intra-class or cluster correlation coefficient (ICC) [57,58]. In order to adjust the sample size for this, the crude sample size calculated above needed to be multiplied by the design effect. The cluster size was ten, as there were ten participants in each team, and we assumed the ICC to be 0.05 [58]. Design effect = 1 + (cluster size – 1) × ICC → design effect = 1.45. Accordingly, the sample size was then 64 × 1.45 = 92.8 participants. We therefore planned to include 100 participants in the experimental and control groups (50 in each group) each of which consists of five teams of 10 participants in each arm. Statistical methods for the primary and exploratory outcome of the hypotheses are laid out in Table 2, and also the statistical methods are described. The intervention was delivered in teams, which means that participants were clustered within teams. Since observations from individuals in the same team are potentially correlated we will use generalized estimating equations (GEE) [59] in the parametric analyses to take this cluster effect into account. The statistical analysis will be adjusted for health-care professional groups. The experimental group (participants or teams in ISS) will be compared against the control group (participants or teams in OSS) for all analyses. The results will be expressed by means with standard deviations and confidence intervals, as well as by medians with percentiles. Associated *P*-values and effect sizes will be reported.

For the interval scale data, linear regression will be used to analyze changes between the experimental and the control group from baseline to peak. GEE will be used to take the clustered nature of the data into account. Non-parametric statistical analyses will be used for the ordinal scale data. Medians and percentiles will be reported and the Mann–Whitney U test will be used. Individual responses to the evaluation questionnaire are measured on a Likert scale and will be treated as ordinal data and analyzed at the item level.

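### The pre-training MCQ and SAQ scores are collected but not used in the stated comparisons; adding them as covariates would gain precision at no cost

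*Protocol article*

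**What the plan says.** In the Protocol article, Table 1 (under Trial interventions) lists two MCQ sittings: "Training day start of day" and "Training day end of the day". The section Primary outcome then defines the contrast from the second sitting alone: the group means "were tested at the end of the training day and will be compared".

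The SAQ follows the same pattern. Under Exploratory outcomes, "SAQ was applied approximately 1 month prior to and approximately 1 month after the training day", but the dimension means "from the experimental and control group will be compared 1 month after the training day".

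Table 2 names ANOVA for both outcomes and classes both as interval data. The section Sample size estimation adjusted for clustering adds GEE to allow for teams, and one adjustment: "The statistical analysis will be adjusted for health-care professional groups". It also says that, for interval data, regression will be used for changes from baseline to peak. No sentence names the pre-training MCQ or SAQ score as a covariate.

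**The concern.** The person's own earlier score on the same instrument is usually among the strongest predictors of the later score. Here it is already measured, yet the stated comparisons give it no role. Two things follow. First, variance that the earlier score could explain stays in the residual, so the confidence interval is wider than it need be in a small trial with ten teams. Second, if one arm happens to start with better-informed members of a given profession, part of that difference passes into the end-of-day contrast, because adjustment for profession cannot remove imbalance within professions.

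The article states the time point, the contrast, the method and a covariate, so this is a stated analysis choice that can be improved, and not simply a detail left for a fuller plan.

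**Working it through.** **Inputs from the article** (Sample size calculation; Sample size estimation adjusted for clustering): SD 24 points, difference 17 points, two-sided 5%, power 80%, ICC 0.05, teams of 10, five teams and 50 participants per arm.

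**Input not in the article:** the pre/post correlation r. Assumed 0.3, 0.5 and 0.7.

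**Step 1. The plan's own figure.** Per arm, n = 2 × (1.96 + 0.8416)² × 24² / 17² = 31.3, rounded up to 32, so 64 in total. Design effect = 1 + 9 × 0.05 = 1.45, and 64 × 1.45 = 92.8, planned as 100. The stated numbers reproduce. They use the full SD with no reduction for baseline, which agrees with a post-only comparison.

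**Step 2. Standard error of the post-only contrast.** Total variance is 24² = 576. Between-team variance = 0.05 × 576 = 28.8; within-team variance = 0.95 × 576 = 547.2.

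SE² = 2 × (28.8/5 + 547.2/50) = 2 × (5.76 + 10.944) = 33.41, so SE = 5.78.

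**Step 3. Add the baseline score.** Teams are formed at random, so baseline is cautiously allowed to explain only within-team variance: SE² = 2 × (5.76 + 10.944 × (1 − r²)).

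| Assumed r | SE² | SE | Reduction in SE |
|---|---|---|---|
| none | 33.41 | 5.78 | – |
| 0.3 | 31.44 | 5.61 | 3% |
| 0.5 | 27.94 | 5.29 | 9% |
| 0.7 | 22.68 | 4.76 | 18% |

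If baseline instead reduced the total variance with the ICC held at 0.05, the SE would be 5.51 / 5.01 / 4.13. The result therefore depends on what baseline is assumed to explain.

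**Step 4. Compare with the planned model.** Step 2 has no covariates, whereas the plan adjusts for profession. Suppose, purely as an assumption, that profession explains 25% of within-team variance. The planned SE is then √(2 × (5.76 + 10.944 × 0.75)) = 5.29 before baseline is used. Adding baseline with within-profession r of 0.3 / 0.5 / 0.7 gives √(2 × (5.76 + 8.208 × (1 − r²))) = 5.14 / 4.88 / 4.46, a reduction of 3% / 8% / 16%. The within-profession r would itself tend to be lower than the overall r if profession drives part of the correlation.

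**Step 5. Chance imbalance.** If the start-of-day score also had SD 24 (the article gives that figure only for the response), the difference in baseline means would have SD 24 × √(2/50) = 4.8 points. This ignores the balance gained by stratifying on profession, so under that SD it is likely an upper figure.

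**Step 6. The sentence on change.** It could be read to cover MCQ and SAQ, since Table 2 treats both as interval data. But each has a single post-training value and so no peak, while cortisol is defined under Exploratory outcomes as a rise from baseline to peak. Applied to MCQ or SAQ, the sentence would conflict with the post-training comparisons stated for them, and it still names no baseline covariate.

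**The case against.** The strongest reply is that nothing here is invalid. Under randomization the expected difference in end-of-day scores equals the expected difference in change, and the standard error already allows for chance imbalance. That stands. So does the point that stratification by, and adjustment for, profession already recover part of the gain, and that the remaining gain cannot be fixed from the article. It is also fair that a condensed article may leave covariates to a fuller plan; but this one names its covariate and its contrast, and the pre-training score is in neither.

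Three stronger readings are tempting and are not supported:

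- **That a post-only contrast fails to test the hypothesis of improvement in Table 2.** The column sets the experimental group against control, and the Intrinsic Motivation Inventory, measured only once, has a hypothesis of increased score. The wording reads naturally as better than control.
- **That leaving out baseline makes the trial underpowered.** With 100 participants, the plan's normal approximation gives 83.7% post-only. A value of about 73% arises only when the test uses 8 between-team degrees of freedom, and that comparator also omits the planned profession adjustment. The shortfall is a separate matter from baseline.
- **That the model must also include availability.** Allocation was stratified "according to the days they were available for training" as well as by profession, but day terms could use up scarce between-team degrees of freedom. Including them is a trade-off, and no correction is asked for.

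**Conclusion.** The point holds as a free gain in precision, not as an error that invalidates the primary analysis or the sample size. In the illustrative calculation the standard error falls by roughly 3% to 18% for assumed correlations of 0.3 to 0.7. That rests on the article's SD and ICC, on baseline explaining only within-team variance, and on an unadjusted comparator. Against the planned profession-adjusted model the gain may be smaller, and its true size is unknown until the within-profession correlation is seen. The consequence is greatest for the MCQ as primary outcome; the SAQ is exploratory, so less hangs on it.

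**What to change.** Keep the end-of-day MCQ as the primary outcome. Fit the GEE model with arm, start-of-day MCQ score and professional group, with team as the cluster. For each SAQ dimension, use the same model with that dimension's pre-training value as covariate. State that the sentence on change from baseline to peak does not apply to MCQ or SAQ.

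The cost is a line or two in the analysis section. No new data are needed, because both pre-training measurements are already scheduled. The change should be written down before any comparison by arm is seen, so that the adjustment is prespecified.

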### Exploratory outcomes

The “Safety Attitudes Questionnaire” (SAQ) consists of 33 items on a five-point scale that is divided into six dimensions. SAQ was applied approximately 1 month prior to and approximately 1 month after the training day. The mean values on six different dimensions of the SAQ results from the experimental and control group will be compared 1 month after the training day. SAQ is an inventory used in several countries and also applied and validated in a Scandinavian context, and previously tested in Denmark [49-51].

Salivary cortisol (reflecting the hypothalamic-pituitary-adrenal axis activity) was used as a biological marker of stress levels. The Sarstedt Cortisol Salivette Device, provided by Neogen corporation [name] Product no. 402710, was used The analysis will be a duplicate analysis based on the Elisa Technique 405 nm, where 100 ul sample will be extracted and 50 ul in duplication will be used in the ELISA kit. Eight standards in ranges from 0.04 ng/ml up to 10ng/ml will be used in the assay together with a blanc control. The microtitterplate will be read in a dual wavelength set at 450 nm and 650 nm. In calculation of the data, the blanc background will be subtracted from all absorbance values before a non linear fit to the standard curve will be calculated.

The salivary cortisol sample was obtained before the simulation (baseline) and three times in relation to the simulations. The cortisol response will be measured as increased salivary cortisol from individual baseline to peak, and mean response values in the experimental and control group will be compared.

State-Trait Anxiety Inventory (STAI-1) was administered before the simulations started (baseline) and twice following the simulations [52,53]. It will reflect the subjective stress response. The peak level of subjective stress response will be used and mean values in the experimental and control group will be compared.

Cognitive appraisal [31,36,54] was assessed before and after each scenario, using the method described by Tomaka [54]; in other words, primary appraisal was examined by asking the participants to answer the question “how stressful do you expect the upcoming task to be?” Secondary appraisal was measured by asking the participants “how able were you to cope with this task?” The participants indicated their answers on an anchored ten-point Likert scale. An index of cognitive appraisal will be calculated as the ratio of the primary appraisal (task) to the secondary appraisal (resource). If the resources are assessed as being greater than the task demands, the situation is appraised as a 'challenge'. If the task demands were appraised as being greater than the resources, the situation is appraised as a 'threat' [54].

“Intrinsic Motivation Inventory” consists of 22 items on a seven-point scale that is divided into four dimensions. It was administered as a questionnaire approximately 1 week after the training day [27]. The median values in the experimental and control group will be compared.

A questionnaire was administered to evaluate participant perceptions of the simulations and the debriefing approximately 1 week after the training day. This questionnaire included questions on a Likert scale about personal perceptions of the scenario (that is, learning, realism, cooperation between health-care professionals, own role in the team, et cetera) and whether the simulation training scenarios inspired the participants to suggest organizational change proposals (that is, changes in guidelines, practical things, et cetera). The data will be treated as ordinal data at the item level. The median values in the experimental and control group will be compared.

Team performance score will be assessed by independent observers through reviewing video recordings of the scenarios. A validated rating scale “Team Emergency Assessment Measure” developed by Cooper and colleagues [55,56] will be used. The median scores of the performance in the experimental and control group will be compared.

Clinical performance in the simulated setting will be assessed by the independent assessors through the reviewing of video recordings of the scenarios. The assessment score is based on data such as minutes passed from the scenario starts till decision was made about operation, minutes from decision making before operation was initiated, and whether medications such as uterotonics were administered or not. The mean score of the performance in the experimental and control group will be compared.

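### The anxiety score is specified as a peak in two places and, by the general rule for interval data, as a change in a third; cortisol uses a simple change where a baseline-adjusted peak would be at least as precise (minor, exploratory outcomes)

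*Protocol article*

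**What the plan says.** **STAI.** The Exploratory outcomes section of the protocol article fixes the quantity: "The peak level of subjective stress response will be used and mean values in the experimental and control group will be compared". The STAI row of Table 2 gives the matching hypothesis, "Increased peak score in the experimental group", and classes the score as follows: "Will be analyzed as interval data, a Gaussian distribution is expected".

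**General rule.** The statistical paragraph under Sample size estimation adjusted for clustering reads: "For the interval scale data, linear regression will be used to analyze changes between the experimental and the control group from baseline to peak". It adds generalized estimating equations for clustering by team. The only covariate it names is profession: "The statistical analysis will be adjusted for health-care professional groups".

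**Cortisol.** The Exploratory outcomes section says: "The cortisol response will be measured as increased salivary cortisol from individual baseline to peak". Table 2 and the general rule say the same.

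**Timing.** Table 1 schedules STAI and cortisol before and after each of the two simulations. The second STAI series is listed as "Training day before 2. simulation and twice after". The Exploratory outcomes section places the STAI baseline ahead of the simulations, in the plural. The Blinding section says that participants were not blinded.

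**The concern.** Two statements specific to STAI make the outcome a peak level. A general statement makes interval data with a baseline and a peak a change. The general sentence is not limited to cortisol, so an analyst who follows it would analyse a different STAI quantity from one who follows Table 2. If the setting already affects stress at the first measurement, the two analyses do not even estimate the same difference between arms. Higher stress under in situ training is one of the trial's stated hypotheses and part of its proposed route to better learning, so the choice bears on interpretation.

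Cortisol has no contradiction. The question there is efficiency: the plan subtracts the baseline in full, although a regression on the same baseline would use it at least as well.

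**Working it through.** **1. Which outcomes the general rule can reach.** It needs a baseline and a peak. The knowledge test, the safety attitudes questionnaire and the timed clinical measures have no peak. STAI, cognitive appraisal and cortisol do. Appraisal is ordinal in Table 2, which leaves STAI and cortisol. For cortisol the rule agrees with every other statement. For STAI it conflicts with two.

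**2. The plan's own figure.** The article gives no precision figure for STAI or cortisol. Its sample size for the knowledge test reproduces: 2 × (1.96 + 0.84)² × 24² / 17² ≈ 31.3, so 32 per arm and 64 in total. The design effect is 1 + 9 × 0.05 = 1.45, and 64 × 1.45 = 92.8. Applying that design effect to the planned 50 per arm gives an effective 50 / 1.45 = 34.5 per arm, used in step 4.

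**3. Relative variance of the arm difference.** Let r be the baseline-peak correlation. The documents do not give it, so 0.3, 0.5 and 0.7 are assumed, with equal variances at the two times.

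| Analysis | Formula | r = 0.3 | r = 0.5 | r = 0.7 |
|---|---|---|---|---|
| Raw peak | 1 | 1 | 1 | 1 |
| Change | 2(1 − r) | 1.40 | 1.00 | 0.60 |
| Peak adjusted for baseline | 1 − r² | 0.91 | 0.75 | 0.51 |

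The change score therefore needs 1.40/0.91 = 1.54, 1.00/0.75 = 1.33 and 0.60/0.51 = 1.18 times the participants of the adjusted analysis.

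With unequal variances, let k be the ratio of peak SD to baseline SD. The change then has variance 1 + 1/k² − 2r/k, and the adjusted peak stays at 1 − r². At k = 1.5 and r = 0.3 this is 1.044 against 0.91. At k = 1.25 and r = 0.8 both are 0.36, because the slope of peak on baseline, rk, equals 1. The change can tie but cannot win, apart from the one degree of freedom that adjustment costs.

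**4. Power, for scale.** Assume a 0.5 SD effect and 34.5 effective participants per arm, with power = Φ(0.5/√(2v/34.5) − 1.96), where v is the variance from step 3. Raw peak gives 55% at each r. Change gives 42 / 55 / 76%. Adjusted gives 59 / 67 / 83%.

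**5. Simulation check.** Ten teams of 10 were simulated with an intra-class correlation of 0.05 and the peak taken as the larger of two later values. Variance relative to the adjusted analysis at r = 0.3 / 0.5 / 0.7 was 1.14 / 1.45 / 2.16 for raw peak and 1.69 / 1.42 / 1.25 for change. The ordering matches step 3.

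**6. If allocation already moves the baseline.** Assume a true effect on the peak of 0.5 SD, a baseline shift of 0.25 SD and a slope of 0.5. Expected estimates are 0.50 for raw peak, 0.50 − 0.25 = 0.25 for change, and 0.50 − 0.5 × 0.25 = 0.375 for adjusted. The simulation gave 0.51, 0.25 and 0.38. In this case the choice between the two STAI statements halves the estimate.

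**The case against.** The strongest reply is that the general sentence was meant for cortisol. It cannot literally cover all interval data, it echoes the cortisol row of Table 2, and two statements specific to STAI should override a general one. That is a reasonable reading of intent. But the sentence does not name cortisol, and Table 2 classes STAI among the data it covers, so the text still needs restricting.

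A second reply is that the choice of covariates for exploratory outcomes can be left to an analysis plan that is not shown, and that linear regression does not rule out a baseline covariate. This stands in part: regressing the change on arm and baseline gives the same arm coefficient as regressing the peak on them. However, the article does fix the cortisol response as a change and names only professional group for adjustment. That is a stated choice that can be improved, not a gap.

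A third reply is that adjustment may be the worse choice for STAI. Participants knew their setting and the first measure was taken on the training day, so it may already carry anticipatory stress. This stands. In step 6 the raw peak alone recovers the assumed effect.

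A reader might also infer that the measure before simulation 2 will serve as a baseline and pull the result toward no difference. The documents do not say so. Table 1 only schedules that measure, and the wording for STAI points to the one before simulation 1. Nor does regression to the mean bias the change score here: in a randomized comparison it acts on both arms alike in expectation, and the cost is precision.

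**Conclusion.** The inconsistency on STAI is real but narrow: a peak in two places, and a change under a general rule read literally. For cortisol the specification is consistent and valid, but never more precise than the baseline-adjusted peak. The size of that loss rests on an assumed correlation and variance ratio. It runs from 1.18 to 1.54 times the participants at r = 0.7 to 0.3 with equal variances, and falls to nothing where the slope on baseline is 1.

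It would be tempting to conclude that the raw STAI peak wastes the baseline and should be replaced. The documents do not support that: with unblinded participants and a baseline taken on the training day, the raw peak is defensible and should remain the stated analysis. Both outcomes are exploratory, and the primary result, sample size and conduct are unaffected. Severity is minor.

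**What to change.** - **General rule:** restrict the baseline-to-peak sentence so that it does not govern STAI.
- **STAI:** keep the unadjusted peak as stated in Table 2 and Exploratory outcomes. Report beside it the peak adjusted for the value before simulation 1.
- **Cortisol:** replace the change score with peak regressed on arm, the value before simulation 1 and professional group, keeping the planned allowance for team clustering.
- **Baseline:** state that it means the measure before simulation 1. This is a clarification only.

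The cost is wording and one degree of freedom, since every measure needed is already scheduled. The downside is that adjustment may remove part of any anticipatory effect of the setting, which is why the unadjusted STAI peak is kept. For cortisol the switch does not worsen this while the slope on baseline lies between 0 and 1, because the change score subtracts the whole of any baseline shift and the regression subtracts only the slope times that shift.
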